### **9.2.3 Suspected unexpected serious adverse reactions (SUSARs)**

NA.

## **9.3 Annual safety report**

NA.

## **9.4 Follow-up of adverse events**

All AEs will be followed until they have abated, or until a stable situation has been reached. Depending on the event, follow up may require additional tests or medical procedures as indicated, and/or referral to the general physician or a medical specialist. SAEs need to be reported until the end of study within the Netherlands.

## **9.5 Data Safety Monitoring Board (DSMB)**

A Data Safety Monitoring Board (DSMB) will be established. It will be independent from the investigators and the sponsor.

Members of the DSMB:

Dr. [name] (epidemiologist, LUMC)

[name]. [name] (statistician, LUMC)

Dr. [name] (experienced clinician in the field, Radboud UMC/Groningen UMC)

The members are not in any other way involved in the trial and have therefore no conflict of interest with the sponsor of the study.

Members will review the interim analyses for the first 21 participants 6 weeks after surgery, focussing on safety of the surgical procedures.

Termination of the trial will be considered if there are more than 2 patients with facial nerve damage and/or severe hearing loss as a result of surgical damage of the facial canal or posterior canal during the operation. The trial will be stopped in case of futility, when it seems to be unlikely that there is a clinical significant effect based on the results of the interim analysis results.

The advice(s) of the DSMB will be sent to the principal investigator of the study. Should the sponsor decide not to fully implement the advice of the committee, the sponsor will send the

advice to the reviewing METC, including a note to substantiate why (part of) the advice of the committee will not be followed.

During the time when interim analysis takes place, no new participants will be included in this study.

An extensive charter for the DSMB can be found in chapter K5 'Overige documenten' of this dossier.

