|                      | Rinne left            | Positive
Negative                                             |
|                      | Dix Hallpike          | Positive
Negative                                             |
|                      | If positive: side:    | Left
Right                                                    |
|                      | Diadochokinesis       | Normal
Abnormal                                               |
|                      | If abnormal: side     | Left
Right                                                    |
|                      | Eye pursuit movements | Smooth
Abnormal                                               |
|                      | If abnormal: direct   | Left
Right
Up
Down                                      |

An MRI- and CT-scan will be performed and the patient is referred to a vestibular therapist. A PTA, vHIT and calorigram will be performed. Moreover, from the moment of inclusion, the patients starts reporting in de DizzyQuest App. This is a daily questionnaire of 31 questions addressing general functioning. In case of an attack, a short questionnaire is to be filled out. The inclusion and exclusion criteria will be double-checked by the coordinating investigator and if the patient does meet the criteria, the first survey package is sent through email. This survey pack consists of the HADS, DHI, THI, SF-36, EQ-5D VAS, NPQ, VADL, VAP and a questionnaire about expectations of the treatment.

All the pre-operative data is entered in Castor.

 The VAP and VADL are newly developed questionnaires to assess the effect of dizziness and/or balance problems on patients' ability to do things. They are not an outcome measure in this study, but we aim to anticipate on the possibility that the Bárány Society takes the outcomes of questionnaires into account in future studies. These questionnaires are taken for this trial as well, to enable comparison of the results of this study in the future that only use the VAP and the VADL.

In the following weeks, the patient visits the vestibular therapist, who takes the medical history and performs the first measurements. The patient is seen by the anaesthetist for regular pre-operative screening.

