### **8.3.2 Surgical procedure (T=0)**

Surgery takes place either at the site of inclusion, or in the HagaHospital. This depends on preference of the local researcher, and availability of equipment at the site. If surgery is performed at the HagaHospital, the local researcher (who has included and will follow the patient) is welcome to join the surgery. An experienced ENT-surgeon who has performed at least 20 EDB procedures ([name]) will always attend surgery to ensure there are not intraoperative differences that may induce differences in outcome. Moreover, this facilitates blinding of the follow-up surgeon.

The surgical procedure is described in chapter 5 'Treatment of participants', 5.1

Investigational product, subheading 'surgical procedure in EDB group'. The randomisation for a clip or decompression operation will be performed using the automated telephone randomised service from Castor. The outcome of randomisation and placing of clip (only EDB) will be documented in Castor. For the purpose of 'implantenregistratie', all used clips and their LOT-number must be documented. Normally, this registration takes place in the electronic patient files, but for blinding purposes, this will now be documented in a paper notebook. After completion of the trial and debinding, this information will be added to the electronic patient file.

An interim analysis of the data for the first 21 participants 6 weeks after surgery will be performed. The DSMB will assess the results and discuss the outcome, and give advice whether or not to continue the study.

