### **8.3.3 Postoperative procedures**

- One week after surgery (T+1)

One week after surgery, the patient will visit the ENT-surgeon for regular post-operative care. A vHIT will be performed. Moreover, the patient will visit the vestibular therapist whom will commence treatment. A balance test, dynamic visual acuity and gait analysis will be performed. Exercises that should be performed at home by the patient are explained. In the

following weeks, the patients carries these exercises out at home, and visit the vestibular therapist three times with two weeks in between the visits.

As surgery is currently not a normal medical treatment, this visit and these measurements are all extra for this study.

- Three months after surgery (T+2)

At three months after surgery, a follow up visit is planned at the ENT-surgeon. A vHIT is performed. The patients visits the vestibular therapist who performed measurements who finishes treatment and performs measurements. An MRI-scan and PTA are performed. The patients receives a survey package through email, consisting of the DHI, THI, FLS, EQ-5D VAS, SF-36, iMCQ and iPCQ.

This visit and these measurements/tests are all extra for this study.

- Six months after surgery (T+3)

At six months after surgery, a follow up visit is planned at the ENT-surgeon. A vHIT is performed. The vestibular therapist performs measurements. A PTA is performed. The patients receives a survey package through email, consisting of the DHI, THI, FLS, EQ-5D VAS, SF-36, iMCQ and iPCQ.

This visit and these measurements/tests are all extra for this study.

- Twelve months after surgery (T+4)

At twelve months after surgery, the last follow up visit for this trial is planned. A vHIT is performed, as well as a PTA, an MRI-scan and calorigram. The vestibular therapist performs measurements and the patients receives a survey package through email consisting of the DHI, THI, FLS, EQ-5D VAS, SF-36, iMCQ, iPCQ, VADL and VAP. If the patient was in de EDB-group, a CT-scan will be performed to assess if the clip is in place in the patients still suffers attacks. If results are in favour of EDB, and patients still suffer attacks, the patients in the decompression group will be offered EDB surgery.

This visit and these measurements/tests are all extra for this study.

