#### **8.7 Premature termination of the study**

Termination of the study will be considered in the case of more than 2 patients with facial nerve damage and/or severe hearing loss, as a result of surgical damage of the facial canal or posterior canal during the operation.

Depending on the results of the interim analysis, the DSMB can advise to terminate the study.

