## **9. SAFETY REPORTING**

### **9.1 Temporary halt for reasons of subject safety**

In accordance to section 10, subsection 4 of the WMO, the sponsor will suspend the study if there is sufficient ground to assume that continuation of the study will jeopardise patient health or safety. The sponsor will notify the accredited METC without undue delay of a temporary halt including the reason for such an action. The study will be suspended pending a further positive decision by the accredited METC. The main investigator ([name]) will keep the participants informed.

Interim analysis will be performed after surgical treatment of 21 participants. In case of more than 5 adverse events (such as permanent hearing loss, extra hospitalisation after surgery), the METC will be notified. In a serious adverse event, the METC will be informed within the legal requirements (< 24 hour).

Substantial protocol changes will be discussed and presented for approval by METC-LDD.

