### **10.4 Interim analysis**

An interim analysis of the data for the first 21 participants will be performed after 6 weeks follow up of the 21st surgery. The DSMB will discuss the safety of the participants, and advice whether or not to continue the study.

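### The 6-week safety interim comes before the first scheduled postoperative audiogram at 3 months, so the DSMB would see severe hearing loss only incompletely and unsystematically

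*Protocol*

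**What the plan says.** **Timing of the look.** Three sections of the protocol set it:
- Section 9.5: "Members will review the interim analyses for the first 21 participants 6 weeks after surgery, focussing on safety of the surgical procedures".
- Section 8.3.2: "An interim analysis of the data for the first 21 participants 6 weeks after surgery will be performed".
- Section 10.4: "An interim analysis of the data for the first 21 participants will be performed after 6 weeks follow up of the 21st surgery".

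The first two can be read as a 6-week cut for each participant. The third is one calendar date, tied to the 21st operation.

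**What the look judges.** Section 9.5 has termination considered at "more than 2 patients with facial nerve damage and/or severe hearing loss as a result of surgical damage" to the facial canal or posterior canal. Section 8.7 states the same criterion without a date. Section 9.5 also allows stopping for futility on the interim results. Separately, section 9.1 sets a notification rule: "In case of more than 5 adverse events (such as permanent hearing loss, extra hospitalisation after surgery), the METC will be notified".

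**When hearing is measured.** Before surgery, section 8.3.1 states: "A PTA, vHIT and calorigram will be performed". After surgery, section 8.3.3 first lists audiometry at the three-month visit: "An MRI-scan and PTA are performed". It is repeated at 6 and 12 months. The one-week visit has vHIT and the therapist's balance, visual acuity and gait tests, but no audiogram. Between one week and three months only vestibular therapist visits are described.

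**Other routes for hearing loss.** Section 9.2.1 records adverse events that the patient reports unprompted or that staff observe. Section 9.4 allows further tests where an event calls for them.

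**The concern.** The stopping criterion and the measurement schedule do not line up. Hearing loss is one of the two harms the criterion names, but the test that would show it systematically falls about 7 weeks after the 6-week mark.

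Before 3 months, hearing loss reaches the DSMB only if someone notices it and follows it up. That is a weak filter here. Under section 4.2 the affected ear must have had documented low-frequency loss on at least one occasion, at least 30 dB worse than the other ear, in a disease with fluctuating hearing. Section 9.2.1 also lists worsening hearing as part of the natural course. Attributing a loss to surgery needs a baseline-to-postoperative comparison. The baseline half exists for everyone; the postoperative half does not exist for everyone at the look.

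The risk is that a missing audiogram is read as no harm. The criterion is met at three patients, so a few unmeasured participants can matter to the advice.

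**Working it through.** The protocol gives no figure of its own on this point, so there is nothing to reproduce. The check sets the visit schedule against the interim date.

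**Inputs**
- Recruitment: 74 patients in 2 years (section 4.1), taken as 74 operations in 24 months, or 104 weeks.
- Look: 6 weeks after the 21st operation (section 10.4).
- First scheduled postoperative PTA: 3 months, or 13 weeks (section 8.3.3).
- Assumption: operations are evenly spaced.

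**Reading 1: one calendar look, section 10.4**
1. Rate = 74 / 24 = 3.08 operations per month, or 74 / 104 = 0.71 per week.
2. Time from the first to the 21st operation = 20 / 3.08 = 6.5 months.
3. A participant has reached the 3-month PTA at the look only if operated at least 13 − 6 = 7 weeks before the 21st operation.
4. Operations in that 7-week window = 7 × 74 / 104 = 4.98, or about 5.
5. So 21 − 5 = 16 have reached the 3-month PTA and 5 have not: 5 / 21 = 24%.

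The result depends on accrual:

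| Accrual | Reached 3-month PTA | Not reached |
|---|---|---|
| Half the planned rate | 18 of 21 | 3 of 21 |
| Planned rate (74 in 24 months) | 16 of 21 | 5 of 21 |
| 1.33 times (74 in 18 months) | 14 of 21 | 7 of 21 |
| Double the planned rate | 11 of 21 | 10 of 21 |

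**Reading 2: data cut at each participant's own 6 weeks (possible under sections 8.3.2 and 9.5)**

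No scheduled PTA lies between surgery and 6 weeks, so 0 of 21 have one.

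**Illustration of what five unmeasured participants can mean**

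Section 9.2.1 cites permanent hearing loss in less than 4%. Take that bound as 4%, and suppose that only participants with an audiogram can be counted. The chance of seeing three or more cases is

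P(X ≥ 3) = 1 − Σ(k = 0 to 2) C(n, k) × 0.04^k × 0.96^(n − k)

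- n = 21: 0.050
- n = 16: 0.024

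The chance is roughly halved. This is not the operating characteristic of the protocol's rule. The rule also counts facial nerve damage, is limited to severe loss from surgical damage, and can be met by cases found without a scheduled audiogram.

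**After aligning the look with the test**

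If the hearing review waits for the 21st participant's 3-month visit, 21 of 21 can have baseline and postoperative PTA, apart from missed visits. The delay is 7 weeks (about 1.6 months).

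**The case against.** A reader might infer that hearing loss cannot be measured at all at the interim. The documents do not support that. Section 10.4, the dedicated interim section, sets one look after the 21st operation, and by then most participants would already have a 3-month audiogram. The figure of 0 of 21 requires discarding audiograms already collected, and sections 8.3.2 and 9.5 do not say to do so.

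Four further points on the other side stand:
- The criterion covers severe loss from operative injury, not hearing loss in general. Surgical observation bears on such an injury, as may the one-week vHIT where the posterior canal is injured. Severe loss can also be reported and then tested.
- Section 8.7 is undated: "in the case of more than 2 patients with facial nerve damage and/or severe hearing loss" can be met after the interim, so a later audiogram still counts.
- The look is not useless without PTA. Facial nerve injury, CSF leakage and meningitis do not depend on it.
- Section 9.1 is a notification rule with permanent hearing loss as an example. It is not a second stopping criterion.

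A reader might also infer that this is purely a safety look, or that hearing loss is the only lasting harm with a quoted risk. Section 9.5 adds futility, and section 9.2.1 also quotes figures for facial nerve injury and perioperative mortality.

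These points narrow the concern but do not remove it. Reporting and testing on suspicion are not systematic, and the most recently operated participants still reach the only planned DSMB look without a scheduled audiogram.

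**Conclusion.** The point holds as a mismatch between fixed parts of the protocol: ascertainment of severe hearing loss at the interim is incomplete and unsystematic, not absent. Under section 10.4 and even accrual at the planned rate, about 5 of 21 participants (24%) lack a scheduled postoperative audiogram. The range is 3 to 10 of 21 for half to double that rate. All 21 lack one only if data are cut at each participant's own 6 weeks.

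The size rests on evenly spaced operations and on section 8.3.3 being the full schedule of audiometry. Appendix 2 (the detailed visit flow chart) and the DSMB charter were not visible, so an earlier audiogram listed there cannot be excluded. Even then, section 8.3.3 would have to be made to agree with it.

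**What to change.** 1. Reconcile sections 8.3.2, 9.5 and 10.4 into one data-cut rule.
2. Keep the 6-week review for early surgical events, and give the DSMB all PTA available at that calendar date.
3. State that the hearing part is completed, as a supplement to the same review, when the 21st operated participant has had the scheduled 3-month PTA. The DSMB then receives baseline and 3-month PTA for all 21, by arm.
4. State whether the pause in inclusion under section 9.5 applies to the supplement.
5. If Appendix 2 or the charter lists an earlier audiogram, bring section 8.3.3 into line with it.

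**Cost.** Wording changes in the protocol and charter. The hearing part comes about 7 weeks later, which means about 5 further operations (7 × 0.71) before it is reviewed if inclusion continues, or a longer halt if it does not. No new test is needed and no stopping number changes. A 3-month audiogram may still not settle whether a loss is permanent.

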**Study design:** This is a double-blinded, randomized controlled trial. Total duration of the study is 4 years. Minimal study duration per participant is 1-year post surgery. All of the operations will take place in participating centres within a fixed period of 2 years after the first patient is operated. Surgery will be performed by two surgeons simultaneously. One of the surgeons will leave the operating room before the randomisation. This surgeon is blinded to the treatment and will take care of the follow-up. Randomization will be 1:1 stratified for gender and duration of MD (recent onset versus mature MD).

**Study population:** The study will include 74 participants suffering from MD who meet the diagnostic criteria as recently revised in 2015. These patients have not responded to more conservative treatment modalities.

**Intervention:** Participants from both study groups will undergo mastoidectomy with identification of the ED. In the EDB group, the ED will be clipped and in the decompression group, it will not be clipped. All participants receive vestibular rehabilitation after surgery. Follow up visits will take place at 1 week, 3 months, 6 months and 12 months after surgery.

**Main study endpoint:** Proportion of patients who are free of vertigo spells at 12 months post-operative.

**Nature and extent of the burden and risks associated with participation, benefit and group relatedness:** All participants will have ear surgery, repeated testing and

questionnaires and report daily in the DizzyQuest app. Usual risks of surgery apply. We expect patients in both groups to benefit from participation, either because of the effect of the surgical interventions, or because of the considerable placebo effect.

An interim analysis will be performed after 21 participants have undergone surgery to assess surgery related risks and to end the trial if safety of participants cannot be guaranteed.

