#### 4.4 Sample size calculation

The sample size for this RCT was computed using software package PASS 11. The sample size calculation is based on the study performed by Saliba (Saliba 2015), in which complete control of vertigo was reached in 96,5% of the patients who underwent EDB. According to literature, endolymphatic sac decompression is effective in  $\pm 70\%$  of the patients (Brinson 2007, Convert 2006, Durland 2006).

We compare MD participants undergoing an operation with clip (EDB group: A group) independently with MD participants undergoing operation without clip (decompression group: B group). Null hypothesis is that the percentage points difference between groups is nil ( $p_A = p_B$ ), with two-sided alternative hypothesis ( $p_A \neq p_B$ ) and with anticipated 25% percent difference ( $p_A = 95\%$  and  $p_B = 70\%$ ). Power is at least 80%. The chance of a false positive finding for either of the analyses is controlled at the 5% level (family wise error rate). To obtain a power of at least 80% for Fisher's Exact test, the required sample size is 32 in groups A and B (allocation ratio = 1). Loss to follow-up will likely occur in a small percentage of cases ( $n=5$  per arm). No selective loss to follow-up is anticipated and a missing-at-random assumption seems reasonable. Missing outcomes will therefore be imputed using multiple imputation in the main analysis. Two sensitivity analyses will be conducted as well, where missing outcomes will be treated as failures or success, respectively. In this case the sample size would be 37 in group A and B (allocation ratio = 1). The total number of participants would be 74.

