### 10.1 Primary study parameter

The primary outcome is defined as being attack free at 12 months follow-up. The required significance level of findings ( $\alpha$ ) will be equal to or lower than 5%. Any statistical tests will be two-sided. P-values will be presented. Where confidence limits can be estimated, the confidence level will be 95%. All analyses will be performed by intention to treat.

A chi-square test (or Fisher's exact test) will be performed on the primary outcome variable data (number of patients free of vertigo attacks at 12 months post-operatively, in EDB vs endolymphatic sac decompression group).

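### Section 9.5 words a futility stop as mandatory on a 21-participant, 6-week interim that the Summary and 10.4 call a safety review, when nobody has the 12-month outcome

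*Protocol*

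**What the plan says.** Section 9.5 first gives the interim a safety task: "Members will review the interim analyses for the first 21 participants 6 weeks after surgery, focussing on safety of the surgical procedures". It then adds an efficacy consequence of the same look: "The trial will be stopped in case of futility, when it seems to be unlikely that there is a clinical significant effect". That sentence ties the decision to the interim results. It names no outcome, threshold or conditional power.

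Elsewhere the interim concerns safety alone. The Summary gives its purpose as "to assess surgery related risks and to end the trial if safety of participants cannot be guaranteed". Section 10.4 sets the timing, "An interim analysis of the data for the first 21 participants will be performed after 6 weeks follow up of the 21st surgery", and the task, "The DSMB will discuss the safety of the participants, and advice whether or not to continue the study".

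The primary outcome lies much later: "The primary outcome is defined as being attack free at 12 months follow-up" (10.1). Follow-up visits are at 1 week and at 3, 6 and 12 months (Summary, 8.3.3), so there is none at 6 weeks. Attacks are also recorded continuously in the DizzyQuest app. Section 4.4 sizes the trial on 95% v 70% with no allowance for stopping early.

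**The concern.** The protocol contradicts itself on what this interim may decide. Taken at its word, the futility sentence asks the board to judge the 12-month effect of clipping from about ten participants per arm, none of whom has reached 12 months. Six weeks is also inside the 3-month rehabilitation period (5.2). Section 3 expects about 70% of patients to improve after any surgical intervention, with similar placebo effects in both arms, and section 1 notes that weeks or months can pass between attacks. An early comparison of attack-free status therefore says little about the 12-month contrast. At stake is a trial that ends without an answer on weak data, and a loss of power that the sample size does not cover.

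**Working it through.** **The plan's own figure.** The protocol gives no figure for the futility rule. The nearest design figure is 32 per arm for at least 80% power with Fisher's exact test at 95% v 70%, two-sided 5% (4.4). Exact enumeration gives 68.0% at 32 per arm, 77.6% at 37 and 80.7% at 39, so the stated figure does not reproduce under the named test. That is a separate matter and nothing below depends on it.

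**When the interim falls.** Inputs: 74 participants, and "All of the operations will take place in participating centres within a fixed period of 2 years after the first patient is operated" (Summary). Uniform accrual is an assumption.
- Rate: 74 / 24 = 3.08 operations per month.
- 21st operation: 21 / 3.08 = month 6.8.
- Plus 6 weeks (6 / 4.345 = 1.4 months): month 8.2.

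The first participant then has about 8 months of follow-up, so 0 of 21 have the 12-month outcome. For even the first participant to reach 12 months, accrual would have to stretch to (12 − 1.38) × 74 / 21 = 37 months.

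**Precision at the look.** Assume, generously, that the 6-week status already shows the design rates. SE = √[0.95 × 0.05 / nA + 0.70 × 0.30 / nB].
- 10 v 11: √(0.00475 + 0.01909) = 15.4 points; half-width 1.96 × 15.4 = 30.3 points.
- 11 v 10: √(0.00432 + 0.02100) = 15.9 points; half-width 31.2 points.

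Both half-widths exceed the 25-point target.

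**Chance of an unpromising result.** Exact binomial enumeration of the observed difference:

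| True rates | Observed difference | 10 v 11 | 11 v 10 |
|---|---|---|---|
| 95% v 70% | ≤ 0 | 7.8% | 4.5% |
| 95% v 70% | ≤ 10 points | 21.8% | 17.7% |
| 90% v 80% (assumed partial effect at 6 weeks) | ≤ 0 | 33.5% | 22.0% |
| 70% v 70% (no effect) | ≤ 0 | 53.9% | 46.2% |

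A rule of stopping at zero or below would therefore also miss about half of the trials of a treatment with no effect.

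**Power if the rule were obeyed.** Simulation with 37 per arm analysed and an 11 v 10 interim. The stopping thresholds are assumptions. The ranges run from a 6-week status independent of the 12-month outcome to one identical with it.

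| Stop if observed difference is | Power (77.6% without the rule) |
|---|---|
| ≤ 0 | 74 to 76% |
| < 10 points | 69 to 73% |
| < 12.5 points | 56 to 62% |

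**What 6 attack-free weeks mean.** Entry requires more than 3 attacks in 6 months (4.2), so the minimum is 4 / 6 = 0.67 per month. Assuming Poisson attacks, P(none in 42 days) = exp(−rate × 42 / 30.4).
- 0.67 per month: 40%.
- 1 per month: 25%.
- 2 per month: 6%.

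These are the shares of patients with unchanged disease who would look attack free.

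**The case against.** A reader might infer from the mandatory wording that the stop is binding. The documents do not support that. Section 8.7 says the board can advise termination, 8.3.2 and 10.4 also speak of advice, and 9.5 itself lets the sponsor decline the advice with a note to the METC. A reader might also infer that the decision would be little better than chance. The figures do not show that either: at the design rates a difference of zero or less is uncommon, and a cautious board would stop less often still. If it stopped only when the upper 95% Newcombe limit lay below 25 points, it would wrongly stop in 1.9% (10 v 11) or 2.5% (11 v 10) of trials. That threshold is as much an assumption as the others.

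Three further points are fair. Section 9.5 refers to a DSMB charter that is not at hand and may hold a boundary, so the missing threshold is not in itself an error. Under the timing in 10.4, early participants would have more than 6 weeks of data, up to about 8 months. And stopping only for futility does not inflate type I error, so the false-positive rate that 4.4 says is "controlled at the 5% level (family wise error rate") is not threatened. The board is also independent of investigators and sponsor, so early exposure of comparative data is a minor matter.

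What remains is that no charter boundary can create 12-month data at this look or remove the conflict between 9.5 and the Summary and 10.4. The sponsor's right to decline limits the harm, but it would then have to justify to the METC why it was not following a rule in its own protocol.

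**Conclusion.** The point holds in this form: 9.5 attaches a futility stop, in mandatory wording, to an interim that the rest of the protocol reserves for safety and that cannot inform the 12-month outcome. That nobody has reached 12 months rests on roughly uniform accrual over the planned 2 years, and has a wide margin. The false-stop chances of 4.5 to 7.8% (zero or less) and 18 to 22% (at most 10 points) assume the full effect is already present at 6 weeks. With an assumed 90% v 80% at that time, zero or less occurs in 22 to 34%. None of these is the trial's actual false-stop risk, which depends on a threshold the protocol does not state. The 40% attack-free figure applies only at the minimum entry rate under a Poisson assumption.

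**What to change.** Delete the futility sentence from 9.5. State there that the 21-participant interim is for safety only, with no efficacy or futility comparison, as in the Summary and 10.4. Align the DSMB charter if it repeats the rule.

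The cost is one sentence in the protocol and possibly one in the charter. No power is lost, and the unaccounted futility loss goes away. The sponsor gives up an early futility exit, but one that these data could not support. If it still wants such an exit, the alternative is to specify it in full: outcome, timing, threshold, non-binding status and an allowance for the lost power in 4.4.
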